#### Exploratory Primary Outcomes

##### Overview

PTA threshold tests will be performed using an audiometer (Otometrics Conera, Natus Medical Incorporated/GN Otometrics A/S) in a standard soundproof room with background noise less than 30 dB(A) to minimize the influence of human factors on the test results. The patient will be presented with sounds at frequencies ranging from 0.25 to 8 kHz [33,34]. An audiologist will use the audiometer to measure both air conduction and bone conduction hearing thresholds. A shift of more than 30 dB between adjacent frequencies indicates hearing loss. Following these measurements, the audiogram configuration is obtained simultaneously. Hearing loss across all frequencies, represented by a horizontal line with threshold differences of less than 20 dB between frequencies, is classified as a “flat” audiogram type [35].

Tinnitus matching is currently the most objective means of detecting tinnitus. It mainly includes 2 parts [36], as described in Textbox 1.

Parts of tinnitus matching.
**Tinnitus frequency matching**
Tinnitus frequency matching is performed using an audiometer (Otometrics Conera). A pure tone with an intensity similar to the tinnitus sound is presented to the ear opposite to the tinnitus-impacted ear or the more severe side, with the frequency adjusted between 0.25 and 8 kHz. This adjustment continues until the presented pure tone frequency matches or closely resembles the patient’s perceived tinnitus frequency, which is then defined as the tinnitus pitch. For patients who cannot match a pure tone, a narrowband noise frequency is used, and the center frequency of this narrowband noise is defined as the tinnitus pitch. Tinnitus frequencies are categorized as low (<1 kHz), medium (1-4 kHz), and high (≥4 kHz).

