**Methods:**

In this double-center, assessor-blinded, randomized controlled trial, 60 patients with ISSNHL accompanied by tinnitus will be randomly allocated to either the EA group, receiving EA combined with medication, or the control group, receiving standard medication treatment, for a total treatment duration of 4 weeks. Follow-up assessments will be conducted at weeks 2 and 4, and at 1, 2, and 3 months after treatment. The feasibility primary outcomes are recruitment rate, adherence rate, data completeness, and safety outcomes. The primary outcome measures will include pure tone audiometry, tinnitus matching, and the Tinnitus Handicap Inventory, while the secondary outcome measures will comprise speech-recognition thresholds in noise, the Self-Rating Anxiety Scale, and the 36-item Short Form Health Survey Questionnaire.

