**Tinnitus loudness matching**
After determining the tinnitus pitch, the audiologist matches the loudness at this frequency. Starting from the hearing threshold at the tinnitus pitch, the intensity of the test tone is gradually increased in 1-dB increments until it just masks the tinnitus sound. The difference between the measured sound intensity and the corresponding hearing threshold at this frequency is recorded as the tinnitus loudness [37]. Tinnitus loudness is classified into 5 levels based on the World Health Organization hearing loss grading: ≤25 dB, 26-40 dB, 41-60 dB, 61-80 dB, and ≥81 dB [38].

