### Statistical Analysis

All efficacy analyses will follow the intention-to-treat principle, including all randomized participants. Statistical analyses will be performed using SPSS version 22.0 (IBM Corp). Continuous variables, including PTA, THI, SAS, and SF-36, will be reported as means (SDs) for normally distributed data, or as medians (IQRs) for nonnormally distributed data. Tinnitus matching (frequency and loudness) will be treated as a categorical variable and summarized as proportions or percentages.

Baseline PTA distributions for both groups will be reported as means (SD) or medians (IQRs). Differences in baseline hearing loss severity will be assessed using the 2-tailed (unpaired) independent samples *t* test (for normally distributed data) or the Mann-Whitney *U* test (for nonnormally distributed data). If significant differences are identified, group comparisons will be adjusted for hearing loss severity using analysis of covariance to ensure comparability.

Changes in PTA, THI, SAS, and SF-36 across 6 time points (t0, t1, t2, t3, t4, and t5) will be evaluated using repeated measures analysis of variance for normally distributed data, or the Friedman test for nonnormally distributed data. Changes in tinnitus matching across the 6 time points will be assessed using the Cochran *Q* test to detect overall differences. If significant, pairwise comparisons will be conducted using the McNemar test with a Bonferroni correction for multiple comparisons.

Group differences in PTA, THI, SAS, and SF-36 at each time point will be analyzed using the independent samples *t* test (for normally distributed data) or the Mann-Whitney *U* test (for nonnormally distributed data). If baseline hearing loss severity differs significantly, analysis of covariance will be applied to adjust for this covariate. Differences in tinnitus matching at each time point will be evaluated using the chi-square test or Fisher exact test, as appropriate. Statistical significance will be set at α=.05 (2-sided).

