Most studies currently agree that the earlier patients with ISSNHL receive treatment, the better their prognosis. The study by Byl [57] indicated that patients who received medical attention within 7 days of onset had an approximately 56% recovery rate, whereas those who presented after 30 days had a recovery rate of only 27% (also see [58]). The study by Diao et al [59] also demonstrated that the number of days from onset to treatment was an independent prognostic factor, with shorter time intervals correlating with better outcomes. Therefore, all patients selected for this study were within 7 days of onset. The medication treatment protocol for ISSNHL with tinnitus is the same as that for ISSNHL. The inclusion of multiple variables (ie, multiple drugs) in the standard treatment is driven by the complex pathophysiology of ISSNHL. Research indicates that inflammation is likely a key contributing factor, and corticosteroids such as prednisone are used to reduce inner ear inflammation and edema, thereby improving hearing outcomes [60]. Ginkgo biloba extract, known for its circulation-enhancing and antioxidant properties, may help restore cochlear microcirculation [61]. Batroxobin, a snake venom–derived enzyme with fibrinolytic activity, may improve inner ear blood flow by reducing blood viscosity [62]. This combination of drugs is designed to simultaneously target distinct pathological mechanisms, thereby enhancing overall therapeutic efficacy. The rationale for this combined approach is supported by evidence from studies conducted in China. A retrospective study involving 342 patients with total deafness-type ISSNHL found that adding batroxobin to a treatment regimen of Ginaton and glucocorticoids significantly improved hearing recovery outcomes and maintained plasma fibrinogen levels within a safe and prognostically favorable range [63]. This improvement was particularly notable in terms of hemorheological parameters and peripheral blood T-cell subset reactivity. Additionally, a 2023 meta-analysis further corroborated the efficacy of Ginkgo biloba extract as an adjuvant therapy, suggesting it may outperform corticosteroid monotherapy [64]. These findings support the decision to incorporate multiple pharmacological agents into the standard treatment protocol, aligning with the goal of addressing the multifaceted nature of ISSNHL.

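### The tinnitus matching classes have no place for tinnitus that has stopped, so resolved patients leave the pitch comparison and are lost or pooled in the loudness comparison

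*Protocol article*

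**What the plan says.** The abstract (Methods) states: "The primary outcome measures will include pure tone audiometry, tinnitus matching, and the Tinnitus Handicap Inventory". Table 1 lists the same three measures as exploratory, and the Outcome Measures section places them under exploratory primary outcomes, after the feasibility outcomes.

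Textbox 1 fixes the classes.

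- **Pitch:** "Tinnitus frequencies are categorized as low (<1 kHz), medium (1-4 kHz), and high (≥4 kHz"). The only fallback is for a patient who hears a sound but cannot match it to a tone: "For patients who cannot match a pure tone, a narrowband noise frequency is used".
- **Loudness:** "After determining the tinnitus pitch, the audiologist matches the loudness at this frequency". Further, "Tinnitus loudness is classified into 5 levels based on the World Health Organization hearing loss grading", namely "≤25 dB, 26-40 dB, 41-60 dB, 61-80 dB, and ≥81 dB".

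Statistical Analysis treats both parts as categorical and includes every randomized patient in the efficacy analyses. Between arms, "Differences in tinnitus matching at each time point will be evaluated using the chi-square test or Fisher exact test, as appropriate". Change over the six time points is tested with Cochran Q, followed by McNemar tests if Cochran Q is significant.

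Eligibility Criteria require tinnitus at entry, so absence of tinnitus can arise only after randomization.

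**The concern.** The classes describe what the tinnitus sounds like, not whether it is still there. Complete resolution is the best result a tinnitus patient can have, and it is the one state the scheme cannot record.

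If resolved patients drop out of the pitch table, the arms are compared only among patients whose tinnitus persisted. That subgroup is formed after randomization and may be shaped by treatment. Randomization no longer protects the comparison, and it sits badly with the commitment to analyse all randomized patients.

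If resolved patients are given 0 dB for loudness, they share the lowest class with patients who still hear a faint tinnitus, and part of any benefit is hidden.

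The Sample Size section says the pilot is to supply effect sizes for later trials. A measure that cannot separate resolved from persisting tinnitus is a weak basis for that.

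**Working it through.** The plan gives no figure on this point, so there is none to reproduce. The check has four steps.

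**1. Does 'no tinnitus' fit any class?**

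| Part | What a class requires | Classes open to a resolved patient |
|---|---|---|
| Pitch | a matched tone or narrowband noise | 0 of 3 |
| Loudness | a pitch first, then a level above threshold at that pitch | 0 of 5 reserved; 25 dB or less if coded as 0 dB |

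**2. How many patients would have no pitch class?**

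Input from Sample Size: 30 recruited per arm. The resolution rates r are assumptions, because the article gives none.

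Patients without a class = 30 × r(EA) + 30 × r(control).

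- Equal rates of 20%: 6 + 6 = 12 of 60.
- Equal rates of 50%: 15 + 15 = 30 of 60.
- Each 10 percentage points of common resolution removes 6 patients, so a rate of 5% would remove 3.
- Unequal rates of 50% (EA) and 30% (control): 15 + 9 = 24 of 60 (40%). The test then compares 15 EA with 21 control patients, and the 20-point difference in resolution does not enter it.

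**3. What does this do to the planned tests?**

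Simulation of the chi-square test: 4,000 runs, two-sided 0.05, 25 per arm (the planned number before the dropout allowance). Assumptions, none from the article: among patients with persisting tinnitus, pitch is low/medium/high in 20/30/50% and loudness falls in the three lowest classes in 70/20/10%, the same in both arms. The arms differ only in resolution.

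Share of runs with a significant result:

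| Resolved, control vs EA | Pitch, resolved excluded | Loudness, resolved placed in 25 dB or less | Pitch with a 'no tinnitus' class | Resolved vs persisting |
|---|---|---|---|---|
| 20% vs 40% | 5% | 5% | 22% | 36% |
| 30% vs 60% | 5% | 8% | 40% | 62% |
| 20% vs 60% | 5% | 11% | 70% | 85% |
| 40% vs 40% | 5% | 3% | 4% | 6% |

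The pitch test stays at its null rate whatever the benefit in resolution. In the 30% vs 60% row it uses on average 25 × 0.7 = 17.5 control and 25 × 0.4 = 10 EA patients. The loudness test keeps some sensitivity, by an amount that depends on the assumed 70% of persisting patients in the lowest class; with fewer there, pooling would hide less. A normal-approximation formula for the last column gives 34%, 57% and 85% in the first three rows, close to the simulation.

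**4. Do the pitch classes overlap?**

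The medium class runs from 1 to 4 kHz and the high class starts at 4 kHz. A match at exactly 4 kHz, inside the tested range of 0.25 to 8 kHz, meets both definitions.

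**The case against.** The strongest reply is that the article is a condensed account. The case report form (Multimedia Appendix 2) is not shown, a separate analysis plan may exist, and either could hold a code for resolved tinnitus. That is possible. But the article itself fixes the classes and the tests applied to them, and those leave no place for such a code. If one exists, it and its analysis need only be stated.

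Other limits on the point stand, and they rule out stronger readings that a reader might infer.

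- **That resolution will be common.** The Discussion says "patients who received medical attention within 7 days of onset had an approximately 56% recovery rate", but it does not present this as a tinnitus resolution rate. The Introduction says that tinnitus eases more slowly than hearing recovers and may outlast it. Resolution may occur; its frequency is unknown.
- **That a benefit in resolution cannot show at all.** This fits pitch only. If resolved patients are placed at 25 dB or less, anyone who started in a higher loudness class shows a shift. The Tinnitus Handicap Inventory, analysed as a continuous score, can also register resolution.
- **That a main efficacy endpoint fails.** The body labels the measure exploratory, the feasibility outcomes come first, and no power calculation rests on it.
- **That resolved patients will lower the data completeness outcome.** Its definition gives audiometry and the Tinnitus Handicap Inventory as examples of key measures and does not name tinnitus matching.

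One may add that the planned pitch test is two-sided and claims no direction. That is true, but a difference in pitch class would then be hard to read as benefit or harm.

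**Conclusion.** The point holds in a limited form. The stated classes do not place a patient whose tinnitus has stopped, and the 4 kHz boundary belongs to two classes; both follow from the text without any assumption. Taken as written, the pitch comparison is conditioned on a post-randomization outcome, and the loudness comparison either loses resolved patients or pools them with persisting cases.

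The size is uncertain. The counts in step 2 scale directly with a resolution rate that the article does not report, and the rejection rates in step 3 also rest on assumed pitch and loudness distributions. They show the mechanism and its possible scale and do not forecast this trial. The matter should be corrected before analysis, but it does not threaten the feasibility outcomes.

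**What to change.** 1. At every visit, record 'no tinnitus (resolved)' as an observed result, distinct from 'not done'.
2. Recode completed visits from source records where these allow it. The Results section reports 42 patients enrolled and 35 with posttreatment assessments, so this matters now.
3. Compare the proportion resolved between arms with all randomized patients in the denominator. Resolved versus persisting is a binary variable, which also suits the planned Cochran Q and McNemar tests; the three pitch and five loudness classes do not.
4. Report pitch and loudness class descriptively among patients with persisting tinnitus.
5. Define the medium pitch class as 1 to <4 kHz.

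The cost is one code on the case report form and short changes to the outcome and analysis text, with no extra visits or tests. There are two small downsides: pitch class is no longer tested as an efficacy outcome, and some past visits may not be recodable if the records do not separate resolved from not done.

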**Tinnitus loudness matching**
After determining the tinnitus pitch, the audiologist matches the loudness at this frequency. Starting from the hearing threshold at the tinnitus pitch, the intensity of the test tone is gradually increased in 1-dB increments until it just masks the tinnitus sound. The difference between the measured sound intensity and the corresponding hearing threshold at this frequency is recorded as the tinnitus loudness [37]. Tinnitus loudness is classified into 5 levels based on the World Health Organization hearing loss grading: ≤25 dB, 26-40 dB, 41-60 dB, 61-80 dB, and ≥81 dB [38].

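### Tinnitus loudness is recorded in 1-dB steps above the patient's own threshold, then graded on hearing-loss cut-points and analysed only as categories, which discards information the trial already collects

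*Protocol article*

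**What the plan says.** Under Tinnitus loudness matching (Textbox 1), the tone starts at the hearing threshold for the matched pitch and "the intensity of the test tone is gradually increased in 1-dB increments until it just masks the tinnitus sound". The recorded value is a difference: "The difference between the measured sound intensity and the corresponding hearing threshold at this frequency is recorded as the tinnitus loudness". The same paragraph continues: "Tinnitus loudness is classified into 5 levels based on the World Health Organization hearing loss grading", with the levels "≤25 dB, 26-40 dB, 41-60 dB, 61-80 dB, and ≥81 dB".

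The Statistical Analysis section lists PTA, THI, SAS and SF-36 as continuous. Loudness is not among them: "Tinnitus matching (frequency and loudness) will be treated as a categorical variable and summarized as proportions or percentages". Within groups, "Changes in tinnitus matching across the 6 time points will be assessed using the Cochran" Q test, followed by McNemar tests with a Bonferroni correction. Between groups, "Differences in tinnitus matching at each time point will be evaluated using the chi-square test or Fisher exact test, as appropriate". No analysis in dB is described.

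Tinnitus matching is one of three primary outcome measures in the Abstract and appears under Exploratory Primary Outcomes in the Methods. The Sample Size section says that the trial will supply effect sizes for planning larger trials.

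**The concern.** There are two faults, one leading to the other.

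**Scale.** A hearing-loss grading classifies thresholds. The loudness procedure subtracts the threshold and then applies cut-points made for it. Nothing in the article suggests that 25, 40, 60 and 80 dB are meaningful boundaries for a level above threshold.

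**Loss of information.** Whatever the cut-points, reducing a 1-dB reading to five grades and analysing only the grades throws away change within a grade. The lowest grade is 25 dB wide and starts at the floor of the scale. If most patients sit there, real improvement leaves the grade unchanged.

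The tests add to the loss. Chi-square and Fisher tests ignore the order of the grades. Cochran's Q and McNemar, in standard form, need a two-level outcome, and the article defines five levels without a dichotomy.

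At stake is the usefulness of the loudness estimate. Proportions across mismatched grades are a poor basis for planning a later trial on a measure taken in dB.

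**Working it through.** **1. The plan's own figure.** The article gives no power or effect size for loudness, so there is none to reproduce. Its only computed figure is the sample size: 25 per group, 50 in total, and 50 × 1.2 = 60 recruited. The illustration below uses 25 per group and the stated two-sided α of 0.05.

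**2. What follows without any assumption.** From the stated grades:
- 25 → 0 dB: lowest grade before and after, so no change is registered.
- 26 → 25 dB: second grade to lowest grade, so a change is registered.

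**3. Assumed inputs.** The documents give no loudness distribution. Mean, SD and a true group difference of 0.8 SD are therefore assumptions, varied over a range.

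**4. Normal model, split at the lowest grade.** Because readings are whole dB, P(≤25) = Φ((25.5 − mean)/SD). For mean 20 and SD 10:
- controls: Φ((25.5 − 20)/10) = Φ(0.55) = 0.71
- shifted arm, mean 20 − 0.8 × 10 = 12: Φ((25.5 − 12)/10) = Φ(1.35) = 0.91
- exact Fisher power, 25 v 25: 0.33
- t test on dB: noncentrality 0.8 × √(25/2) = 2.83 on 48 degrees of freedom, power 0.79

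| Mean (dB) | Controls ≤25 dB, SD 8 / SD 10 | Fisher power, SD 8 / SD 10 | t test on dB |
|---|---|---|---|
| 10 | 97% / 94% | 0.00 / 0.00 | 0.79 |
| 15 | 91% / 85% | 0.02 / 0.09 | 0.79 |
| 20 | 75% / 71% | 0.28 / 0.33 | 0.79 |
| 25 | 53% / 52% | 0.45 / 0.46 | 0.79 |
| 30 | 29% / 33% | 0.53 / 0.54 | 0.79 |

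**5. Skewed model, all five grades.** Simulated gamma values rounded to 1 dB, 2,000 runs. The Fisher test is used when two grades are occupied and chi-square when three or more are. The fourth column is the share of patients who change grade if every patient's loudness falls by about 0.8 SD.

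| Mean, SD (dB) | Share in fullest grade | Power on grades | Share changing grade | t test on dB |
|---|---|---|---|---|
| 10, 6 | 98% | 0.00 | 1.5% | 0.78 |
| 15, 8 | 90% | 0.02 | 7% | 0.78 |
| 20, 10 | 75% | 0.19 | 18% | 0.79 |
| 25, 12 | 58% | 0.37 | 32% | 0.78 |
| 30, 15 | 44% | 0.47 | 46% | 0.78 |
| 40, 15 | 40% | 0.62 | 64% | 0.79 |
| 50, 20 | 38% | 0.63 | 80% | 0.79 |

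**6. Cross-check.** A normal model on all five grades at means of 30-50 dB gives power of about 0.4-0.55, in line with the skewed model or somewhat below it. In every scenario, power on the grades is below that on dB.

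**The case against.** **The distribution is unknown.** No documented fact places mean loudness at 10-20 dB. The tone must be raised "until it just masks the tinnitus sound", and if it goes to a better-hearing ear the differences could be larger. This stands. A reader might infer that the outcome can hardly show change at all; the documents do not support that. At assumed means of 30-50 dB, power on the grades is about 0.4-0.63: reduced, but not absent.

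**The affected-ear argument.** A reader might also infer that hearing recovery with unchanged tinnitus would raise the recorded loudness dB for dB, so that the arm recovering more hearing looks worse. Likewise, one might argue that with a 60 dB threshold the top two grades need tones above 120 dB. Both suppose that the affected ear is tested. The preceding textbox item, Tinnitus frequency matching, sends the tone to the ear on the other side from the tinnitus, and loudness matching continues that procedure. Its added alternative about the more severe side is ambiguous, and the loudness item does not name the ear. The affected-ear reading is thus possible but not the natural one. It merits a clarification and no more.

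**This is a pilot.** There is no formal power calculation, the feasibility outcomes are descriptive, and PTA and THI are analysed as continuous. So this is not a failed primary test, and the 0.8 SD effect is only illustrative. But the pilot is meant to yield effect sizes, and that is the purpose the grading serves badly.

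**Conclusion.** The point holds on the article's own text: a level above threshold is graded on hearing-loss cut-points, and the analysis is fixed as categorical only. The insensitivity within grades and the mismatch between five levels and tests for two levels need no outside figure.

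The size does need assumptions. Over the range examined, with 25 per arm and a 0.8 SD difference, power on the grades runs from 0.00 to 0.63, against about 0.79 on dB. The loss occurs throughout and is severe only if mean loudness is about 20 dB or less. The harm is confined to the loudness part of tinnitus matching and to the effect-size data it should yield. The change is worth making, but the trial's feasibility aims do not depend on it.

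**What to change.** In Statistical Analysis, move tinnitus loudness to the continuous variables. Compare groups on the recorded dB value, adjusted for its baseline. If grades are kept, use them only as a descriptive summary. Report the presented tone level beside the difference from threshold; the procedure already obtains both.

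In the loudness item of Textbox 1, confirm that loudness is matched in the same ear as pitch, and resolve the ambiguous alternative in the frequency item.

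The analysis change needs no new measurement: it costs a little more analysis and one more descriptive column. The Results section places data compilation and analysis after publication of the protocol, so it can still be made. The ear is different. With 42 enrolled and 35 past their posttreatment assessments, the clarification can document what was done but cannot repair visits where practice varied.
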